#### Qualitative interview study

Participants will be sampled from two groups: (1) Up to 48 participants who complete the NHS CHECK 6-month follow-up survey; and (2) Up to 12 members of staff (from participating Trusts) who are involved in implementing staff support programmes, who do not need to have completed any NHS CHECK surveys. Group 1 will be sampled according to sex, ethnicity, age (a cut-off of 50 years will be used to dichotomise participants into younger or older groups), and occupational role. Balancing these demographic factors, four discrete groups of HCWs will be sampled, with 12 in each group: (i) Those who used support programmes and found them helpful; (ii) Those who used support programmes but did not find them helpful; (iii) Those who heard about support programmes but did not use them; and (iv) Those who had not heard about support programmes. We will endeavour to include a diverse range of participants in Group 2, but this will be dependent on those involved in staff support in participating Trusts.

Participants in Group 1 will be recruited first, and what they tell us will inform subsequent interviews with those in Group 2.

### Inclusion criteria

Inclusion criteria for each part of the study are as follows.

#### Longitudinal cohort study

Participant must:

Be an NHS-affiliated member of staff, working at, or with (eg, volunteer or student), the participating NHS Trusts and/or Nightingale Hospitals during the COVID-19 pandemic.Be aged 18 and over.Be able to give informed consent to take part in research.Be able to understand and communicate in English.Have access to an email address to facilitate survey registration and receive follow-up survey links.

#### Diagnostic interview study

Participants must meet the criteria for the cohort study, and must also:

Have completed the baseline NHS CHECK Survey as an NHS member of staff based at a participating Trust; including the relevant PTSD survey measures if being administered the CAPS-5.Have indicated in the baseline survey that they consent to be contacted for participation in further research.Have access to a phone for the interview.Have scored ≥4 on the GHQ to meet caseness for probable common mental disorders or ≥14 on the PCL-6 to meet caseness for probable PTSD.

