**Ethics and dissemination:**

Ethical approval for the study was granted by the Health Research Authority (reference: 20/HRA/210, IRAS: 282686) and local Trust Research and Development approval. Cohort data are collected via Qualtrics online survey software, pseudonymised and held on secure university servers. Participants are aware that they can withdraw from the study at any time, and there is signposting to support services if participants feel they need it. Only those consenting to be contacted about further research will be invited to participate in further components. Findings will be rapidly shared with NHS Trusts, and via academic publications in due course.

Strengths and limitations of this studyThe longitudinal cohort design addresses the lack of long-term data on this population, and the current predominance of cross-sectional evidence available.The availability of Trust Human Resources data means we will be able to calculate response rates, and weight the data appropriately.The diagnostic interview component of the study will allow us to establish the true prevalence of mental disorders, which can be inflated by the measures used in most mental health and well-being cohort studies.The qualitative interviews will give deeper insight into the support programmes that healthcare workers (HCWs) find most helpful, and provide ideas for Trusts to improve their offer to staff.The three components of the study give breadth and depth lacking in much of the mental health and well-being research currently available, but there is a risk of overburdening already stretched HCWs.

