##### Consent

Potential participants will be able to view the information sheet via the study website, then register and provide informed consent if they wish to complete the survey. Paper copies of the participant information sheet (PIS) and consent form can be provided on request. Questions can be emailed to the research team via a dedicated study email address. Participants will provide consent to take part in the study, including baseline and follow-up surveys, and can opt in to consent to be contacted about any linked future studies (eg, trials of support interventions). We will make clear that participation is voluntary and that participants can withdraw at any time without detriment. Due to the rapid publication of data summaries, it will not be possible to withdraw data from published work, but we will not use withdrawn data in any future publications.

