#### Diagnostic interview study

##### Recruitment

Participants meeting the inclusion criteria will be emailed with an invitation to participate in the study, including the PIS. Participants who respond to the email indicating their interest will receive a follow-up email containing a link to a digital calendar where they can select an interview slot suitable to them using an assigned participant Identification (ID), which will be confirmed by email by the research team. Participants who do not select a time slot within 10 days of the booking emails being sent will be prompted to respond if still interested in participating, and followed up by phone calls or texts to confirm interest or withdrawal.

Participants will be able to email the research team via the dedicated study email address with any queries.

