### Analysis plan

#### Longitudinal cohort study

Response weights will be calculated for each Trust, generated using a raking algorithm based on age, sex, ethnicity and role (using Trust population data obtained from Human Resources), with missing demographic data imputed using multiple imputation (for the purposes of weighting only). Trusts with response rates under 5% will be dropped from the analysis. Representativeness of the sample will be described using frequencies and percentages, and descriptive statistics given for each variable to summarise participants (frequencies and weighted percentages for categorical variables, mean and SD for continuous variables). We will examine differences between participants completing only the short survey, compared with those completing both the short and long surveys. We will summarise the weighted prevalence of the primary and secondary outcomes, stratified by sociodemographic and occupational factors. We will explore potential longitudinal associations between sociodemographic characteristics and occupational factors with the outcome measures (eg, GHQ-12, GAD-7, PHQ-9, AUDIT, PCL-6, MIES). Three-level random intercept linear or logistic (depending on the distribution of the outcome) regression models will be used to account for the hierarchical structure of the data, considering observations from baseline, 6-month follow-up and 12-month follow-up at level 2 and NHS trusts at level 3. We will use a measure of pressure on Trusts as the key exposure (eg, ratio of beds in use to staff numbers, ie, those not on sick leave), plotting levels of this exposure over time (aggregated at the Trust level), before partitioning the data into meaningful periods corresponding to burden level over the baseline data collection period (April 2020 to January 2021). We will plot all measures over time to look at patterns between this exposure and outcome levels, and use three-level random intercept logistic and linear regression models, as appropriate, to explore factors associated with outcomes in each period.

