#### Diagnostic interview study

This study will validate the screening questionnaires used for general distress and PTSDs using diagnostic interviews with the CIS-R and the CAPS-5, respectively. Participants for the validation studies will be randomly selected from those with non-missing screening scores in a 50% ratio of caseness or otherwise. Sample sizes were obtained by simulation studies (n=250 and 100, respectively, for the CIS-R and CAPS-5 diagnostic interviews). Sensitivity, specificity, and positive and negative predictive values will be calculated. If possible, prevalence values for the population at risk will be calculated using population weightings (which will be derived from sex, age and ethnicity variables in an attempt to ensure representativeness in the sample population). Sensitivity analyses will be undertaken to account for missingness if necessary.

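### Diagnostic interviewees select themselves from the baseline respondents, and prevalence weights built on sex, age and ethnicity alone cannot correct for participation that varies with symptom severity

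*Protocol article*

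**What the plan says.** Three places in the Protocol article make the interview sample self-selected.

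- Inclusion criteria, Diagnostic interview study: participants must "Have indicated in the baseline survey that they consent to be contacted for participation in further research". The abstract (Ethics and dissemination) repeats this: "Only those consenting to be contacted about further research will be invited to participate in further components".
- Study procedures, Longitudinal cohort study, Consent: the agreement is voluntary and separate from consent to the surveys. Participants "can opt in to consent to be contacted about any linked future studies".
- Study procedures, Diagnostic interview study, Recruitment: there is a further step after invitation. "Participants who respond to the email indicating their interest will receive a follow-up email" with a link for booking a slot.

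The Analysis plan for the Diagnostic interview study describes the selection in one sentence: "Participants for the validation studies will be randomly selected from those with non-missing screening scores in a 50% ratio of caseness or otherwise". It mentions neither the opt-in nor uptake. The weights for prevalence are ones "which will be derived from sex, age and ethnicity variables in an attempt to ensure representativeness in the sample population". The only related safeguard is "Sensitivity analyses will be undertaken to account for missingness if necessary".

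The cohort weights are "generated using a raking algorithm based on age, sex, ethnicity and role". They add role but no symptom measure.

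**The concern.** Establishing the true prevalence of disorder by interview is part of the primary objective. The Introduction offers it as the answer to surveys that overstate prevalence.

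Drawing names at random does not make the people interviewed a random sample of those screened, because two voluntary steps lie between the screen and the interview. Sampling half cases and half non-cases controls only the binary screen. The case half still spans GHQ-12 scores 4 to 12 and the non-case half 0 to 3, and the chance of a disorder on the CIS-R can be expected to rise with the score inside each half. If more distressed staff are keener, or less able, to take part, the interviewed severity mix shifts. The positive predictive value (PPV) and the disorder rate among screen-negatives (1 − NPV) shift with it. Weights on sex, age and ethnicity do not see this, and more interviews would not shrink it. The same argument applies to the PCL-6 and the CAPS-5.

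**Working it through.** **The plan's own figure.** The article expects 250 CIS-R interviews to give prevalence to within ±6%, from a simulation whose inputs are not given. At an assumed 95% level:

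- Simple random sample: 1.96 × √(0.5 × 0.5/250) = 6.2 points.
- Two-phase design, 125 per half, case share W: 1.96 × √[W²·PPV(1−PPV)/125 + (1−W)²·NPV(1−NPV)/125]. With W = 50%, PPV = 40% and 1 − NPV = 10%: 1.96 × √[(0.25 × 0.24 + 0.25 × 0.09)/125] = 5.0 points. Over W 30–60%, PPV 40–60% and 1 − NPV 5–20%, the settings tried gave 3.7 to 5.9.

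So ±6% is plausible. These formulas contain sampling error only; no selection term enters.

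**Size of a severity-related shift.** Every input here is assumed.

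- Disorder probability rises linearly from 20% at GHQ 4 to 70% at GHQ 12, and from 2% at 0 to 15% at 3.
- The probability of opting in and being interviewed is 0.15 at score 4, and its odds change by a factor f per point.
- The case share is 50% and is correctly weighted back, so only selection within halves remains.
- Scores within each half are either flat, or declining in proportion to 9, 8, …, 1 (cases) and 4, 3, 2, 1 (non-cases).

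In each half the interviewed disorder rate is Σ(share × participation × disorder probability) / Σ(share × participation). Prevalence = 0.5 × PPV + 0.5 × (1 − NPV). Figures are in %.

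| Scores | f | PPV | 1 − NPV | Prevalence | Bias (points) |
|---|---|---|---|---|---|
| Flat | 1 (truth) | 45.00 | 8.50 | 26.8 | 0 |
| Flat | 0.85 | 39.03 | 7.81 | 23.4 | −3.3 |
| Flat | 0.9 | 41.13 | 8.04 | 24.6 | −2.2 |
| Flat | 1.1 | 48.11 | 8.95 | 28.5 | +1.8 |
| Flat | 1.2 | 50.30 | 9.38 | 29.8 | +3.1 |
| Declining | 1 (truth) | 36.67 | 6.33 | 21.5 | 0 |
| Declining | 0.85 | 32.65 | 5.80 | 19.2 | −2.3 |
| Declining | 0.9 | 34.00 | 5.97 | 20.0 | −1.5 |
| Declining | 1.1 | 39.10 | 6.71 | 22.9 | +1.4 |
| Declining | 1.2 | 41.09 | 7.08 | 24.1 | +2.6 |

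With flat scores and the extreme slopes, the bias is −3.9 to +3.5 points at 60% cases and −2.3 to +2.2 at 30%.

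The extreme slopes are steep. Between scores 4 and 12, 0.85⁸ = 0.27 (odds 3.7 times lower) and 1.2⁸ = 4.3 (odds 4.3 times higher).

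**Cost of weighting on the score.** The Kish design effect in a half is Σ(share × participation) × Σ(share / participation). It is 1.03 to 1.16 in the case half and 1.01 to 1.03 in the non-case half.

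**The case against.** **The frame may not be contradicted at all.** The opt-in is stated in the eligibility criteria and in the abstract, so the Analysis plan can be read as drawing from opted-in respondents who also have a score. This stands. A reader might infer that the article contradicts itself, or treats interviewees as drawn from everyone screened. The text supports only that the Analysis plan does not repeat the restriction and does not adjust for it.

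**Modelling of non-response belongs in an analysis plan that is not shown, and the article is a condensed account.** This is partly right. Prevalence is offered only if possible, and sensitivity analyses for missingness are foreseen. But the article does name the weighting variables, and the screening score is not among them. The sensitivity analyses are conditional and unspecified, and they would not alter the main estimate. Sensitivity, specificity and predictive values carry no such reservation.

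**Existing controls help.** The sample is split on caseness and stratified by site, ethnicity, sex and age (Study population and sample). GHQ-12 and PCL-6 are given again shortly before the interview. These controls deal with coarse selection and let interviewees be described. They do not adjust for severity within a half.

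**The size is conjecture.** Agreed: it depends on a score distribution and on slopes that the article does not give. A reader might also infer a bias larger than ±6%, by supposing that participation depends on the disorder itself. With 50% cases, PPV 40% and 1 − NPV 10%, a 1.5-fold participation ratio gives 0.5 × 0.50 + 0.5 × 0.143 = 32.1% against 25%, or +7.1 points. Nothing in the article supports that ratio. Selection of that kind would also be only partly corrected by weighting on the score.

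**Conclusion.** The point holds in a limited form. Interviewees pass two voluntary steps, and the stated weights contain nothing that would correct for severity-related participation within the caseness halves. Whether such a bias occurs, in which direction and how large, cannot be told from the article. Under the assumptions above, at 50% GHQ cases, it is about 1.4 to 2.2 points for odds factors of 0.9 or 1.1 per GHQ point. At the steepest slopes it is −2.3 to −3.3 or +2.6 to +3.1 points, at most about half of the stated ±6% and additional to it.

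A reader might infer that the shift can be fully removed with data already held. That goes too far: weighting on the score reduces selection explained by the score and leaves the rest. The change is still worth making, because the estimate serves a primary objective and the score of everyone in the screened group is by definition available.

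**What to change.** In the Analysis plan for the Diagnostic interview study:

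1. State the frame as respondents with a screening score who opted in to further contact.
2. Build one weight that brings interviewees back to all baseline respondents with a screening score. Include the full score, or score bands, within each caseness half, together with age, sex and ethnicity. This weight should replace, not multiply, any weight that already carries the 50:50 sampling fraction or the demographic adjustment; otherwise those are counted twice.
3. Keep the model sparse. CAPS-5 has up to 100 interviews, about 50 per half, so use PCL-6 score bands and few demographics; terms for 18 Trusts and role would overfit. PCL-6 is in the optional long survey, so respondents with a PCL-6 score should be the first target population.
4. Report the score distribution of interviewees against all respondents in the same half, and say that selection on severity not captured by the score remains.

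The cost is a few lines of wording and a modest weighting step, with no more interviews. Intervals widen slightly: a design effect of 1.16 in the case half multiplies that half's standard error by √1.16 = 1.08, and further variables add somewhat more.

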#### Diagnostic interview study

Participants will be up to 350 HCWs who have completed the baseline NHS CHECK survey.

Up to 250 participants will be purposively sampled according to their responses to the General Health Questionnaire (GHQ) in the short survey module;^13^ half will meet caseness and half will not meet caseness. These participants will be administered the Clinical Interview Schedule-Revised (CIS-R).^14^ The number of CIS-R interviews (n=250) has been chosen balancing precision and cost. Based on a simulation study, we anticipate that 250 interviews will allow estimation of CIS-R prevalence of common mental disorders to within ±6%.

Up to 100 HCWs will be sampled according to their responses to the 6-item PTSD Checklist civilian version (PCL-6)^15^ in the long survey module; half will meet caseness and half will not meet caseness. These participants will be administered the Clinician-administered PTSD Scale (CAPS-5).^16^ This sample size was calculated as the necessary number to achieve a valid estimation of PTSD prevalence.

Sampling for the CIS-R and CAPS-5 groups will be stratified to ensure representation from each of the 18 participating sites in the NHS CHECK Study, as well as to ensure ethnic, sex and age breakdown that resembles respondents of the baseline survey.

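### The interview study's inclusion criteria admit only screen cases, contradicting its half-case, half-non-case design and undermining the prevalence and accuracy estimates

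*Protocol article*

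**What the plan says.** Four parts of the Protocol article bear on who is interviewed.

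- **Inclusion criteria, Diagnostic interview study.** The list is introduced with "Participants must meet the criteria for the cohort study, and must also", so each item is a requirement. The last item is "Have scored ≥4 on the GHQ to meet caseness for probable common mental disorders or ≥14 on the PCL-6", the second threshold being the one for probable PTSD.
- **Study population and sample, Diagnostic interview study.** For the CIS-R, "Up to 250 participants will be purposively sampled according to their responses to the General Health Questionnaire (GHQ) in the short survey module". For the CAPS-5, "Up to 100 HCWs will be sampled according to their responses to the 6-item PTSD Checklist civilian version (PCL-6") in the long module. Of each group the text says that "half will meet caseness and half will not meet caseness".
- **Analysis plan, Diagnostic interview study.** Participants are to be "randomly selected from those with non-missing screening scores in a 50% ratio of caseness or otherwise". Sensitivity, specificity and both predictive values are planned, with population prevalence if possible.
- **Study procedures, Diagnostic interview study, Recruitment.** "Participants meeting the inclusion criteria will be emailed with an invitation to participate in the study".

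The sample-size text expects 250 CIS-R interviews to give prevalence to within ±6%. The aims section makes determining true prevalence of disorders part of the primary objective.

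**The concern.** A score of 4 or more on the GHQ, or 14 or more on the PCL-6, is the article's own definition of caseness in its Measures section. Making that score a condition of entry means that everyone eligible is a case on at least one screen. The sampling and analysis sections need the opposite for half of each group, and nothing exempts that half from the criterion.

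The criterion also has practical force, because invitations go to people who meet it. The part of the sample it shuts out is the part that shows how much disorder the screens miss. Without it the study cannot turn screening results into a true prevalence, which is what the article presents as its advantage over questionnaire-only surveys.

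**Working it through.** **Planned numbers.** 250/2 = 125 GHQ non-cases for the CIS-R and 100/2 = 50 PCL-6 non-cases for the CAPS-5; 250 + 100 = 350, the stated total. Under the inclusion criterion, the number of eligible people negative on both screens is 0.

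**The plan's own figure.** Let W be the share screening positive, PPV the disorder rate among screen-positives, and f = 1 − NPV the rate among screen-negatives. Then

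- prevalence = W·PPV + (1 − W)·f
- 95% half-width = 1.96·√[W²·PPV(1 − PPV)/125 + (1 − W)²·f(1 − f)/125]

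The article gives neither the simulation inputs nor the confidence level, so I assumed 95%, W from 0.30 to 0.60, PPV from 0.30 to 0.60 and f from 0.05 to 0.20.

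- Smallest (W = 0.30, PPV = 0.30, f = 0.05): 1.96·√[(0.0189 + 0.0233)/125] = 3.6 points.
- Largest (W = 0.60, PPV = 0.50, f = 0.20): 1.96·√[(0.0900 + 0.0256)/125] = 6.0 points.

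The stated ±6% is therefore compatible with a 125/125 design, although it cannot be reproduced exactly.

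**Reading A: each threshold applies to its own instrument.** All 250 CIS-R participants are GHQ cases.

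- There are no true or false negatives in the sample. Sensitivity is 100% and specificity 0% by construction, and NPV is undefined.
- PPV is estimable: 1.96·√[PPV(1 − PPV)/250] gives ±5.7 points at PPV = 0.30 and ±6.2 at PPV = 0.50.
- With f unobserved, prevalence lies anywhere from W·PPV (f = 0) to W·PPV + (1 − W) (f = 1). With W = 0.50 and PPV = 0.50 this is 0.25 to 0.75.
- The half-range is (1 − W)/2: 35 points at W = 0.30 and 20 points at W = 0.60. More interviews would not narrow it.

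**Reading B: the literal *or*.** A GHQ non-case may enter the CIS-R group if positive on the PCL-6, and a PCL-6 non-case may enter the CAPS-5 group if positive on the GHQ. The negative half need not be empty, but everyone in it is symptomatic on the other screen. If their disorder rate is f* rather than f, prevalence is shifted by (1 − W)(f* − f).

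As an illustration only, take W = 0.50, PPV = 0.50, f = 0.10 and f* = 0.20:

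| | True (f = 0.10) | Estimated (f* = 0.20) |
|---|---|---|
| Prevalence | 0.30 | 0.35 |
| Sensitivity | 0.83 | 0.71 |
| Specificity | 0.64 | 0.62 |
| NPV | 0.90 | 0.80 |

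The prevalence error, 0.50 × 0.10 = 5 points, is about as large as the whole stated margin. The documents give no figure for f*, so the actual size is unknown.

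**The case against.** The best defence is that this is a slip of wording and the design is intact. The sampling section says twice that half will be non-cases. The analysis section names a sampling frame that is not confined to cases and plans specificity and NPV, which presuppose non-cases. The bullet reads like a threshold definition placed in the wrong list. Another bullet already asks for the PTSD measures from anyone given the CAPS-5, which would be largely redundant if a PCL-6 score of 14 or more were required. A team working from the sampling and analysis sections would recruit correctly.

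Most of this stands as an account of what was intended, and it shows which text to change. It does not remove the contradiction. Eligibility criteria are the rule that staff apply, the recruitment text refers to them, and nothing in the article ranks one section above another.

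Two qualifications also stand. The zero refers to people negative on both screens, whereas 125 and 50 count negatives on one screen; the loss of everything except PPV therefore belongs to Reading A, and Reading B gives a selected negative group instead. The analysis section also makes population prevalence conditional on feasibility, but the aims section still places true prevalence within the primary objective.

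**Conclusion.** The concern holds, and the criterion is wrong as written. It contradicts the sampling and analysis sections and, if followed, excludes everyone negative on both screens. Under one reading, sensitivity, specificity and NPV cannot be estimated and prevalence is bounded only to within ±20 to ±35 points for W between 0.60 and 0.30, against the stated ±6%. Under the other, all of them rest on an unrepresentative negative group, probably with too much disorder in it.

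The existence of the conflict depends on no assumption. The sizes depend on the assumed W, PPV and f, because the simulation inputs are not given. The half-and-half design and the sample size of 250 are not in question: with the negative half kept, the precision claim is plausible. Because part of the primary objective depends on it, this must be corrected.

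**What to change.** Replace the last bullet of the diagnostic interview inclusion criteria with:

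> Have a non-missing baseline GHQ-12 score (CIS-R group) or PCL-6 score (CAPS-5 group). GHQ ≥4 and PCL-6 ≥14 define the sampling strata, with half of each group drawn from each stratum.

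This carries the analysis section's own selection rule into the eligibility list. If invitations have already been sent, the sponsor should also state which rule was applied, since that decides whether the reported specificity, NPV and prevalence can be interpreted.

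The cost is one bullet of protocol text. The totals of 250 and 100 interviews do not change.
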